### Analysis strategy

#### Analysis of clinical efficacy

Intention-to-treat and per-protocol analysis will be used. Analysis will include the description and ‘head-to head’ comparison between the two groups. Descriptive statistics of the included variables (mean and 95% confidence interval for normally distributed quantitative variables; and median and interquartile range for abnormally distributed quantitative variables) will be performed. To confirm the main hypothesis, all variables will be compared (t0-tk) using an analysis of variance (ANOVA) and post-hoc tests or Kruskal-Wallis non-parametric tests. Finally, more sophisticated multivariate analysis, including multilevel regression, will be used. The effect size of improvement and the number needed to treat (NNT) in each arm will be estimated.

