Finally, the comorbidity of depression and chronic pain is extremely high in PC (56%) and reaches even higher rates in secondary care (50–69%) [25]. Given the high level of disability associated with the comorbidity of chronic pain and depression, and regardless of the direction of this association, national guidelines and consensus [15, 25] indicate the need to perform an objective assessment of pain in patients with depression by means of validated instruments. In addition, they establish that an integral therapeutic intervention should be considered, contemplating pharmacological and non-pharmacological treatments. The most common pain affects the lumbar skeletal muscle and is of mechanical origin, and almost the entire population suffers from it sometime in their life [26]. Together with depression, they lead the ranking of global disability caused by diseases [27]. Clinical guidelines recommend a treatment that includes education, physical exercise, physiotherapy and acupuncture [28]. However, there is not enough evidence on long-term results or on the superiority of any of these treatments over others [29–31]. A recent systematic review with meta-analysis has found long-term superiority of cognitive behavioural therapy compared to other therapies in relation to pain, disability and quality of life [32]. Despite the advantages that they could bring, there are no studies on the application of ICTs to either multimorbidity or any of the medical conditions included in this study [33].

The aim of this study is to evaluate the effectiveness in PC of a blended low-intensity psychological intervention applied through ICTs in the treatment of multimorbidity in PC (depression and type 2 diabetes / low back pain) in an RCT. Our main hypothesis is that the treatment-as-usual intervention, enhanced through the delivery of low-intensity psychological therapy by ICTs, will be more effective for the improvement of the symptomatology of multimorbidity in PC, in relation to a group with treatment-as-usual only, measured at 6 months after completion of the treatment.

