### Sample size

The sample size of this study was based on the possibility of detecting differences between the intervention programme versus treatment-as-usual, for a difference in the main variable of at least 0.5 standard deviations. This effect size was obtained from other studies, and it is considered a clinically relevant criterion [34, 35]. Assuming equal variance between the groups, a power of 80%, and a level of significance of 5%, 63 subjects were estimated for each group. To be able to compare the subjects treated with the specific intervention versus those receiving with treatment-as-usual only, as well as depending on the conglomerate to which they belong (each disease group), 4 groups were estimated with 63 subjects in each one, with a total of 252 subjects. An experimental mortality loss of 15% was estimated [36, 37], so the required size was finally 300 subjects (100 at each PC centre).

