#### Cost-utility analysis

Cost-effectiveness will be explored through the calculation of incremental cost-effectiveness ratios (ICERs) for the intervention group using the iTAU group as the control. To estimate the ICER (ratio between incremental costs and incremental effectiveness) the following equation will be used:$$ ICER=\frac{Cost\kern0.17em active\kern0.17em intervention\ group\hbox{-} Cost\ control\ intervention\ group}{Effectiveness\ or\ Utility\ active\ intervention\ group\hbox{-} Effectiveness\ or\ Utility\ control\ intervention\ group\ } $$

Cost-utility will be explored through the calculation of incremental cost-utility ratios (ICURs), which are defined as the ratio between incremental costs and incremental effects measured on QALYs [58]. QALYs will be approximated by using the area-under-the-curve technique.

Data collection will be performed using Excel software and statistical analysis will use SPSS (SPSS Inc., Chicago, IL, USA) software version 20, licensed by the University of Malaga.

Frequency and proportions will be used for descriptive statistics of categorical or qualitative variables. For quantitative variables, the mean and standard deviation will be obtained.

Inferential statistical analysis will use the Chi-square test for qualitative variables, one-way ANOVA test for qualitative and quantitative variables and Student’s t-test for quantitative variables. In all cases, statistical significance will correspond to a value of *p* < 0.05.

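### The main hypothesis is to be confirmed by comparing all variables at p < 0.05, although the plan defines one composite at one time point, sized for a single 5% test

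*Protocol article*

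**What the plan says.** Four places in the protocol article point to a single confirmatory question:

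- The Abstract and the end of the Background state one main hypothesis: the intervention added to improved usual care does better than improved usual care alone, "measured at 6 months after completion of the treatment".
- Main outcome defines the primary outcome as one composite of depression, diabetes and pain measures.
- Sample size is calculated "for a difference in the main variable of at least 0.5 standard deviations".
- The same section fixes the error rates: "Assuming equal variance between the groups, a power of 80%, and a level of significance of 5%, 63 subjects were estimated for each group".

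Two places point elsewhere:

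- Analysis of clinical efficacy: "To confirm the main hypothesis, all variables will be compared (t0-tk) using an analysis of variance (ANOVA"), with post-hoc tests, or Kruskal-Wallis as the non-parametric alternative. The composite and the 6-month visit are not mentioned there. Multilevel regression follows as a later, more sophisticated analysis, with no stated role in confirming the hypothesis.
- The closing paragraph of Cost-utility analysis: "In all cases, statistical significance will correspond to a value of" p < 0.05.

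The efficacy section also says: "The effect size of improvement and the number needed to treat (NNT) in each arm will be estimated".

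**The concern.** This is a conflict within the printed text, not a detail left to an analysis plan. A later plan that named one confirmatory test would have to contradict the sentence that ties confirmation to all variables.

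As written, a reader cannot tell which result confirms the hypothesis. A significant difference on any of several instruments, at any of three visits, could be presented as confirmation, and the 5% level used in the sample size would then not describe the error rate of the trial's main claim. Letting the method be either ANOVA or Kruskal-Wallis, with no rule tied to the primary outcome, adds one more open choice.

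The NNT wording is a smaller error. An NNT is the inverse of a risk difference between two arms, so it has no value within each arm.

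**Working it through.** **1. Reproduce the plan's own figure.** Inputs from Sample size: difference 0.5 SD, power 80%, significance 5%. Sidedness is not stated; two-sided reproduces the result.

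n per group = 2 × (1.960 + 0.842)² / 0.5² = 62.8, rounded up to 63. Four disease-by-arm groups give 4 × 63 = 252. With 15% loss, 252 / 0.85 = 296.5, so 297; the plan's 300 agrees closely. The calculation therefore assumes one test at two-sided 5%.

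**2. Count the comparisons.** Table 2 lists seven outcome instruments at baseline and every follow-up: PHQ-9, glycosylated haemoglobin, FPS-R, Roland-Morris, SF-12, EQ-5D-3L and OFS. Follow-ups are post-treatment, 3 months and 6 months. So 7 × 3 = 21. Adding the composite at each visit gives 24.

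**3. Chance of at least one false positive when there is no effect.** For k independent tests at two-sided 5%, it is 1 − 0.95^k. The hypothesis is directional, so only a result favouring the intervention could confirm it; that chance is 1 − 0.975^k. For a single test the two benchmarks are 5% and 2.5%.

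| Tests | Any direction | Favouring the intervention |
|---|---|---|
| 1 (composite at 6 months) | 5% | 2.5% |
| 7 (one per instrument) | 30% | 16% |
| 21 (7 × 3 visits) | 66% | 41% |
| 24 (composite added) | 71% | 46% |

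**4. Allow for correlation.** The documents give no correlations, so these are assumptions: 0.3 to 0.7 between outcomes and 0.5 to 0.8 between visits. Simulating 21 jointly normal test statistics (200,000 draws per setting) gives:

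- any direction: 56% (0.3 between outcomes, 0.5 between visits) down to 32% (0.7 and 0.8);
- favouring the intervention: 30% down to 16% at the same settings.

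**5. After the fix.** One confirmatory test keeps the error at 5%, and 63 per group stays valid. Keeping all 21 comparisons confirmatory with a Bonferroni correction would mean 0.05 / 21 = 0.0024 per test and 121 per group.

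**6. Baseline adjustment, for scale only.** If the comparison were of change scores, the variance in SD units would be 2(1 − r), against 1 − r² with baseline as a covariate, where r is the baseline-to-follow-up correlation (not given; r = 0.4 assumed). Variances are 1.20 and 0.84. For 0.5 SD:

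- 63 per disease-by-arm cell: power about 72% against 86%;
- 126 evaluable per arm (252 / 2), the main two-arm comparison: 95% against 99%.

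**The case against.** The strongest defence is that the article never says one significant variable is enough to confirm the hypothesis. The phrase t0-tk may mean the span of visits, so a repeated-measures ANOVA with one test per variable, and the mention of post-hoc tests fits that reading. The p < 0.05 sentence stands under the cost-utility heading. Glycosylated haemoglobin and the pain measures apply to one disease group each, so no patient contributes to every comparison.

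Part of this stands. The 21-test count is one reading, and the figures for favourable results are the fairer ones. But one test per instrument still gives 30% (16% favourable) if independent. Kruskal-Wallis compares independent groups and cannot serve as a repeated-measures test. The threshold sentence applies to all cases and follows general remarks on software and descriptive statistics. Condition-specific measures remain separate routes to a positive claim at trial level.

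A reader might infer more than the article supports:

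- **Unadjusted change scores as the fixed method.** No covariate is named, but t0-tk is ambiguous. Baseline adjustment is a gain in efficiency, not a correction of bias.
- **A large loss of power in the main comparison.** The 72% against 86% belongs to a within-disease comparison of 63 per cell, not to the two arms.
- **Analysis of complete pairs only.** The article states intention-to-treat and gives no complete-case rule. In the Discussion, 40% dropout refers to previous studies and 30% is a target; the sample size assumes 15%.
- **Invalid standard errors from ignoring centre.** Multilevel regression is planned, and with individual randomization in blocks by centre, omitting centre generally makes the test conservative.

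**Conclusion.** The point holds for the confirmatory rule. The article defines one hypothesis, one composite and one visit, then ties confirmation to all variables and sets p < 0.05 throughout. If any of the 21 comparisons could be used to claim success, the chance of a false positive in favour of the intervention is about 16–30% under the assumed correlations and 41% under independence, against 2.5% for a single two-sided 5% test. In either direction it is 32–56% and 66%, against 5%. The narrowest reading, seven independent tests, gives 16% and 30%.

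These sizes rest on the count from Table 2, on correlations that the article does not give, and on the premise that a significant result on any variable could be taken as confirmation, which the wording leaves open but does not state. The contradiction itself depends on none of them. The NNT phrase is a separate misstatement and does not affect the confirmatory test.

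**What to change.** In Analysis of clinical efficacy:

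- State that the sole confirmatory test is the intention-to-treat between-arm difference in the composite at 6 months after treatment, at two-sided 5%.
- Replace the choice between ANOVA and Kruskal-Wallis with one pre-specified model. The multilevel regression already planned can take this role, with centre and disease group included. Add the baseline value where the outcome is a continuous score. Several components are responder criteria that already contain change from baseline, so a composite built from them has no obvious baseline value, and the model must suit the form in which the composite is finally defined.
- Label all other variables and visits secondary, with no confirmatory claim.
- Replace the NNT for each arm with one between-arm NNT and its confidence interval.

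The cost is wording in the protocol and analysis plan. No extra patients, visits or measurements are needed, and the sample size of 63 per group stands.

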#### Main outcome

According to the objectives of the study, the primary outcome will be a composite that considers the following variables:

Depressive symptom severity will be assessed via the Patient Health Questionnaire (PHQ-9) [40] using the Spanish validated version [41]: Percentage of patients with reduction ≥2 points. The PHQ-9 [40], validated Spanish version [41] is one of the questionnaires that assess the intensity of depression most widely used in pharmacological and psychological studies. It is a brief and self-applied scale whose objective is to help diagnose depression (DSM-IV criteria) and determine its severity. Similarly, it is also useful to monitor changes experienced by patients over time. It will be taken four times: at baseline, post-treatment, and at 3-month and 6-month follow-ups.

Control of diabetes will be measured by VR d = glycosylated haemoglobin (% ≤ 7 or % with a decrease of 0.50 baseline), HbA1c, fasting capillary blood glucose, weight (kg), height (cm), waist circumference (cm), and abdominal diameter (cm).

Pain intensity and physical limitation will be measured. Pain intensity will be assessed via the Faces Pain Scale – Revised (FPS-R) [42], a self-report measure in which the patient scores the chosen face with 0, 2, 4, 6, 8, or 10, counting from left to right, where 0 = no pain, and 10 = very much pain. Disability will be assessed via Roland-Morris Scale [43]: This scale is designed to reliably determine the level of physical disability resulting from non-specific low back pain. In this regard, ‘physical disability’ is defined as the limitation in the performance of daily activities between 0 (absence of disability for back pain) and 24 (maximum possible disability). A change in score only has clinical relevance if it is of 2 or more points, although the optimal threshold is between 3 and 4 [44–46]. VR d = % with decrease ≥2 points.

The composite would be weighted to give 1/3 or 1/2 to each of the main measures of depression, diabetes and pain, obtaining an aggregate score. The calculation of the weighting of the composite variables would be performed by means of multiple regression.

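### The confirmatory sentence prescribes a t0-tk comparison of all variables, which does not fit the primary composite, and no listed test is designated for the composite at 6 months

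*Protocol article*

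**What the plan says.** **Confirmatory rule** (Analysis of clinical efficacy): "To confirm the main hypothesis, all variables will be compared (t0-tk) using an analysis of variance (ANOVA) and post-hoc tests". The stated alternative is Kruskal-Wallis. The same paragraph also plans other analyses:
- a group comparison: "Analysis will include the description and ‘head-to head’ comparison between the two groups"
- a further model: "Finally, more sophisticated multivariate analysis, including multilevel regression, will be used"
- for each arm, an effect size and an NNT.

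**Primary outcome** (Main outcome): a weighted composite of depression, diabetes and pain measures. Its stated criteria are:
- PHQ-9: "Percentage of patients with reduction ≥2 points"
- Diabetes: "glycosylated haemoglobin (% ≤ 7 or % with a decrease of 0.50 baseline"
- Roland-Morris: "VR d = % with decrease ≥2 points"

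FPS-R pain intensity is listed in the same section as a 0-10 score, with no response criterion. The component weights are given first as 1/3 or 1/2, then as something to be derived by multiple regression.

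**Contrast and time point** (end of Background, and Abstract): intervention against improved usual care, 6 months after treatment ends.

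**The concern.** The plan states a confirmatory rule, and that rule does not match the endpoint it is meant to test. The PHQ-9 and Roland-Morris criteria exist only after baseline has been subtracted, so they have no value at t0. The HbA1c criterion is mixed: its attainment part exists at t0, its decrease part does not. Under the t0-tk rule an analyst must therefore do one of three things:
1. Difference the raw scales, which leaves the composite untested.
2. Invent a t0 score for the composite and difference that, which for two components subtracts baseline twice.
3. Set the t0-tk wording aside and compare the 6-month composite between arms.

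The text does not choose. If the choice is made once data are available, the declared primary outcome may not be what confirms the hypothesis, and the options can lead to different conclusions.

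**Working it through.** **1. The plan's own figure.** Sample size uses a 0.5 SD difference, 80% power and 5% significance. Taken as two-sided, n per group = 2 × (1.960 + 0.842)² / 0.5² = 62.8, so 63. Four groups give 4 × 63 = 252, and 252 / 0.85 = 296.5, so 297, which the protocol rounds to 300. The figures reproduce. They rest on a between-group difference in means of one main variable, not on a baseline-to-follow-up comparison of all variables.

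**2. Does each component have a t0 value?**

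| Component | Criterion | Value at t0? |
|---|---|---|
| PHQ-9 | fall of at least 2 | no |
| Roland-Morris | fall of at least 2 | no |
| HbA1c | at or below 7, or fall of 0.50 | first part yes, second part no |
| FPS-R | none given | yes, as a 0-10 score |

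A composite with some parts defined at t0 and others undefined has no coherent t0 value.

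**3. One patient.** Take a diabetic patient with HbA1c at or below 7 at both visits and no PHQ-9 response, with weights of 1/2. The composite at 6 months is 1/2 × 0 + 1/2 × 1 = 1/2. With change criteria scored 0 at t0, the t0 composite is also 1/2 and the difference is 0. On raw HbA1c the change may also be zero, although the patient counts as a responder.

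**4. How many patients this touches.** Share = (share diabetic) × (share of those at or below 7 at baseline). The documents give neither. Assuming 40-60% and 20-60%, the range is 0.4 × 0.2 = 8% to 0.6 × 0.6 = 36%. Each of these patients has a differenced score half the 0-1 range below the composite score.

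**5. Effect on the verdict (simulation).** From the protocol: 150 per arm. Assumed: half diabetic; weights of 1/2; independent components; no dropout; PHQ-9 response 40% against 50%; Roland-Morris 35% against 45%; HbA1c response in those above 7 at baseline 25% against 35%; remaining at or below 7, 85% against 90%. A t-test on the 6-month composite was compared with a t-test on the composite minus its t0 value.

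| Share at or below 7 at baseline | Verdicts differ at p<0.05 |
|---|---|
| 20% | about 12% |
| 40% | about 17% |
| 60% | about 20% |

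- Power was about 62-68% for both versions.
- With no treatment effect, both rejected in about 5% of trials and disagreed in about 4-6%.
- These figures let the diabetic share vary by chance between arms. Fixing it at exactly half per arm lowers disagreement to about 12-16%.
- Adjusting the 6-month composite for disease group and baseline HbA1c control gave power of about 68-70%, against 63-68% unadjusted.

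**6. What the open choice could cost.** The chance that at least one of two tests rejects is (first rate + second rate + disagreement) / 2. With no effect this is (5 + 5 + 4) / 2 = 7% to (5 + 5 + 6) / 2 = 8%. It applies only if the more favourable version were picked after seeing both.

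**The case against.** A reader might infer that the plan has no executable test of its primary outcome. The document does not support that. It plans a head-to-head comparison of the two groups, and the Background fixes the contrast and the time point. ANOVA or Kruskal-Wallis on a 6-month aggregate score needs no t0 composite. Multilevel regression is planned too, and Cost-utility analysis lists a chi-square test. Run between arms on a two-component composite, ANOVA, Kruskal-Wallis and chi-square all held type I error at 4.9-5.1%.

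The t0-tk notation can also mean change from t0 to follow-up compared between arms. That reading suits the two criteria defined as falls. It does not suit HbA1c at or below 7, and applied to the scales themselves it still leaves the composite untested.

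It is also too broad to say that the components have no baseline value: the HbA1c attainment part and FPS-R do.

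The simulated disagreement should not be over-read. It depends on scoring change criteria 0 at t0, which the protocol nowhere prescribes, and on assumed rates. Two valid, correlated tests at about 65% power often disagree: covariate adjustment alone changed the verdict in about 7-11% of the same trials.

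Finally, model detail commonly sits in an analysis plan that is not shown. That excuses missing detail. It does not excuse a published confirmatory sentence that points at the wrong quantity.

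**Conclusion.** The point holds as a misalignment. The sentence that claims to confirm the main hypothesis names neither the composite nor 6 months, and its t0-tk form does not fit criteria that already encode change or that can be met without change. Suitable between-arm tests are available, but none is designated. The 12-20% disagreement in verdicts is conditional on the assumed rates, equal weights of 1/2 and the zero score at t0. It shows that the choice can matter, not that either version is biased or weaker. The correction is worth making because it is nearly free and closes a choice that should not be open once data exist.

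**What to change.** In Analysis of clinical efficacy, state that the main hypothesis is tested by one between-arm contrast of the composite at 6 months post-treatment, with no t0 subtraction. Take it from a single linear model adjusted for disease group, baseline PHQ-9 and the baseline somatic measure. Keep t0-tk comparisons of the continuous scales as supportive, and drop post-hoc tests for the two-arm contrast, where there is only one pair to compare.

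Main outcome must be settled too, or the test cannot run: choose between the fixed weights of 1/3 or 1/2 and the regression-derived weights, and say whether FPS-R enters the composite and by what response rule.

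The cost is a few sentences, written before outcome data are examined. No new measurements or patients are needed.

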#### Descriptions of costing procedure

Data collection on the use of health and social services will be collected through the CSRI-Spanish version [39, 50]. Costs of the study will be estimated from the healthcare and societal perspectives during the previous six months (before baseline), and during the six months of follow-up. Direct health care costs will be calculated by adding the costs derived from pharmacological consumption, use of health services and clinical tests, and costs incurred by the staff running the intervention.

The cost of medication will be calculated by determining the price per milligram during the study, according to the databases of the Spanish Ministry of Health and Consumer Affairs, including value-added tax. The total cost of medication will be calculated by multiplying the price per milligram by the daily dose in milligrams and the number of days of treatment. The main source of the unit cost data for medical tests and health services is the OBLIKUE database of health care costs [54]. The OBLIKUE database contains information about Spanish health service costs and is derived by systematic reviews of the literature. Indirect costs (lost productivity) will be calculated considering sick leave days and multiplying them by the minimum daily wage in Spain for 2018. Finally, total costs will be calculated by adding direct and indirect costs. The unit costs will be expressed in euros (€), based on 2018 prices.

The two interventions in this study will be conducted by government agencies and financed by the Carlos III Health Institute; their implementation will not incur additional costs for the Spanish National Health Service. Therefore, costs associated with the interventions in the study will not be included.

The economic evaluation of this study will follow the general guidelines for conducting pharmacoeconomic analyses in Spain. It will also follow the Guidelines of the International Society for Pharmacoeconomics and Outcomes Research (ISPOR) [55] and the Consolidated Health Economic Evaluation Reporting Standards (CHEERS) [56].

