#### iTAU at primary care level

All the patients included in the study (whether they receive the Internet-delivered psychological intervention or not) will be also treated by their GPs. In practice, treatment-as-usual in PC is any kind of treatment administered by the GP to the patient with depression. However, this treatment in primary care will be improved because the participating GPs will receive a training programme on the widely used Spanish Guide for the Treatment of Depression in Primary Care, which is based on the NICE guidelines on subject [15]. In case of suicide risk, severe social dysfunction or worsening of symptoms, it is recommended that patients are referred to mental health facilities [38]. For both groups, the use of health and social services – including consultations with professionals, pharmaceutical use and other resources, will be registered using the Client Service Receipt Inventory (CSRI) [39].

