##### CSRI Spanish version [39, 50]

Questionnaire for collecting information about the use of health and social care services and other economic impacts (such as time off work due to illness). The variant used in this study was designed to collect retrospective data on service utilization during the 12 previous months.

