#### Utility scores

Utility scores will be obtained from two health-related quality of life questionnaires EuroQol 5D and SF-12. QALYs will be calculated based on these scores using the Spanish EQ-5D tariffs [57]. Along with EQ-5D utility scores, scores recorded on the EQ VAS will also be used as an outcome for the analysis.

The perspective used in our analysis will be twofold: the social perspective, to include all costs and quality of life, and the perspective of the Spanish health system.

The time horizon of the study is six months, so it will not be necessary to apply a discount factor to the costs.

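### The stated total-cost rule has no social-service term, although the social perspective is said to cover all costs and the CSRI records social-service use

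*Protocol article*

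**What the plan says.** **What is collected.** Under 'Descriptions of costing procedure' the protocol article states: "Data collection on the use of health and social services will be collected through the CSRI-Spanish version". The section 'iTAU at primary care level' applies this to both arms ("For both groups, the use of health and social services"). The description of the CSRI among the secondary outcomes also names social care, together with time off work, and Table 2 gives health and social service use as the instrument's assessment area.

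**What is promised.** The costing section announces a healthcare and a societal perspective. 'Utility scores' defines the latter as "the social perspective, to include all costs and quality of life".

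**What is summed.** The costing section gives one rule:
- Direct part: "Direct health care costs will be calculated by adding the costs derived from pharmacological consumption, use of health services and clinical tests", to which the cost of the staff delivering the programme is added.
- Indirect part: days of sick leave, "multiplying them by the minimum daily wage in Spain for 2018".
- Total: "total costs will be calculated by adding direct and indirect costs".

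**What it is priced with.** Ministry of Health databases are named for medication, and the OBLIKUE database is named as the main source for tests and health services. No source is named for social services.

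**What is said about intervention costs.** The direct part lists the staff cost. Later in the same section, the costs of the two interventions are left out on the ground that they add nothing to the health service's expenditure.

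**The concern.** The data collection and the definition of the perspective both include social care, but the only total written down does not. Two participants alike in everything except social-service use would receive the same total cost. Any effect of the programme on social-care use, in either direction, would then drop out of an analysis presented as covering all costs.

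The written societal total would differ from direct health care cost only by the sick-leave term, which is itself priced at the legal wage floor. The Discussion presents cost-effectiveness as an aim and the inclusion of an economic evaluation as a strength of the trial, so the rule behind the societal ratios should match its own definition.

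**Working it through.** The article gives no unit cost, wage in euros, resource use or expected ICER, so there is no stated figure to reproduce. The check is a comparison of components, followed by algebra with assumed values.

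**1. Components side by side**

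| Component | Recorded or described | In the stated sum | Price source named |
|---|---|---|---|
| Medication | yes | yes | yes (Ministry databases) |
| Health services and tests | yes | yes | yes (OBLIKUE as main source) |
| Social services | yes (CSRI) | **no** | **no** |
| Sick leave | yes (CSRI) | yes | yes (2018 minimum daily wage) |
| Intervention staff | described | listed, later excluded | not stated |

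Social services are the only CSRI category named in the article that is missing from both the sum and the price sources.

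**2. Effect on cost levels.** If social services make up a share s of an arm's true societal cost, the written total is too low by s. For assumed shares of 5%, 10% and 20%, the shortfall is 5%, 10% and 20%. This only restates the assumption.

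**3. Effect on the ratios.** 'Cost-utility analysis' builds the ICER and ICUR on between-arm differences (intervention minus iTAU). Let dH be the difference in health care cost, dS the difference in social-service cost, dL the difference in sick-leave days, and w the daily wage as a multiple of the minimum.

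- As written: incremental cost = dH + dL
- With all terms: incremental cost = dH + dS + w·dL
- Error of the written rule = −dS − (w − 1)·dL

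Neither dS nor dL has a sign fixed in advance. Illustration in units of one minimum daily wage, with assumed dH = 5 and an assumed QALY gain of 0.02 (ICUR = incremental cost / 0.02):

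| dS | dL | w | As written: cost (ICUR) | All terms: cost (ICUR) |
|---|---|---|---|---|
| −2 | 0 | 1 | 5 (250) | 3 (150) |
| +2 | 0 | 1 | 5 (250) | 7 (350) |
| 0 | −3 | 1.5 | 2 (100) | 0.5 (25) |
| 0 | −3 | 2 | 2 (100) | −1 (−50) |
| 0 | +3 | 1.5 | 8 (400) | 9.5 (475) |
| 0 | +3 | 2 | 8 (400) | 11 (550) |

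In the first two rows, leaving out social services makes the programme look too costly in one case and too cheap in the other. The last four rows show the same for floor pricing: it overstates incremental cost if the programme reduces sick leave and understates it if sick leave rises.

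**4. Size of the wage effect.** If mean pay is k times the minimum, the sick-leave cost and any between-arm difference in it are understated by 1 − 1/k. For assumed k = 1.25, 1.5, 2 and 2.5 this is 20%, 33%, 50% and 60%.

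**5. Intervention staff.** The programme is delivered in one arm only, so its staff cost enters dH in full under the first statement and not at all under the later one. The two statements give different incremental costs from the same data.

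**The case against.** **The wording leaves room.** The itemised sum is labelled direct health care costs, while the total adds direct costs, a wider term. OBLIKUE is called the main source, not the only one. A condensed article may leave itemised unit costs to a fuller document. This reading is possible, and it is why the point asks for reconciliation and does not assert that social care will in fact go uncosted. But no other place in the article supplies the missing term, and the sum as printed does not match the stated scope.

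**The wage rule is a legitimate choice.** This stands. The valuation is openly fixed in advance and is conservative. Covering all costs concerns which categories are counted, not the unit price, so a reader who infers that the minimum wage contradicts the social perspective goes beyond the text. It warrants a sensitivity analysis, not replacement.

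**The direction is unknown.** This also stands. A reader might infer that costs too low in each arm mean an ICER and ICUR that are too low, favouring the programme. The documents do not support that: the ratios rest on differences, and the error can take either sign.

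**The size is assumed.** True. The mismatch does not depend on the assumed shares or wage ratios, but no euro amount can be attached to it.

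**Conclusion.** The point holds as an internal mismatch. The social perspective is said to cover all costs and the CSRI records social services, yet the stated total has no term or price source for them. Followed literally, each arm's societal cost level is understated wherever social services are used, and the incremental societal cost is misstated by the whole between-arm difference in social-service cost, with unknown sign. It would be too strong to say that the ICER or ICUR is understated, or that the two perspectives cannot be told apart: lost productivity still separates them.

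Minimum-wage pricing is a secondary matter. It shrinks any sick-leave cost difference by 20–60%, on the assumption that mean pay is 1.25 to 2.5 times the minimum. The conflicting statements on intervention costs bear on the same sum and must be settled with it.

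The conclusion rests on reading the printed rule as complete. It concerns the economic evaluation only and leaves the primary efficacy outcome untouched. The change is worth making because it is cheap.

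**What to change.** In 'Descriptions of costing procedure', state two sums in place of one:

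- Health-system cost = direct health care costs.
- Societal cost = direct health care costs + (CSRI social-service use × unit cost) + lost productivity.

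Name the source of the social-service unit costs. In the same edit, reconcile the listing of intervention staff costs with the later exclusion of intervention costs. Otherwise the direct health care term in both sums stays ambiguous.

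Keep sick leave at the 2018 minimum daily wage in the base case, as pre-specified, and add a sensitivity analysis at the mean Spanish wage.

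**Cost.** Wording, a set of social-service unit costs and a published wage figure. No new data collection is needed, since the CSRI already records the use. The downside is a little more costing work and somewhat more variable societal costs.
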